##### Autonomic nervous system

As previously mentioned, emotions involve psychophysiological processes, and thus generate changes in variables such as heart rate and blood pressure [68] or galvanic skin response [69].

A number of studies have reported higher heart rate variability (HRV) in older adults as self-reported positive emotion and well-being increase [70], with high HRV being associated with greater emotional well-being and better emotion regulation [71–73]. Then, the health benefits of positive emotions on health may derive from reduced cardiovascular activation associated with decreased sympathetic nervous system (SNS) activation and an increase in activation of the parasympathetic nervous system (PNS) [74]. Furthermore, positive emotions facilitate cardiovascular recovery following negative emotions [75]. Low heart rate has been associated with pleasant or relaxed emotional states, while heart rate accelerations occur in response to intense emotional states, sexual arousal or mental effort [76].

Furthermore, electrodermal activity (EDA), or galvanic skin response (GSR), has been associated with SNS activity [77, 78]. Studies such as that by Codispoti et al. reported higher skin conductance response to exposure to emotional pictures [79]. The use of EDA is highly effective in measuring the level of an individual’s emotional arousal, regardless of the emotional valence of the stimuli, since it is able to quantify changes in the SNS [80]. Various studies have identified changes in EDA (increase in peaks) following exposure to images taken from the IAPS [81].

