#### Processing and statistical analysis of objective variables

##### Heart rate variability (HRV) and electrodermal activity (EDA)

Data processing

Cardiovascular and electrodermal activity variables will be measured through blood volume pressure (BVP) and skin conductance, respectively, using the Empatica E4 device. Alternations of the BVP waveform are highly correlated with heart ventricular depolarization and repolarization, thus being suitable to measure heart rhythm [96]. BVP and SC will be recorded at a sampling rate of 100 Hz and 4 Hz, respectively. Once data are acquired, BVP and SC signals will be processed to reduce noise. To avoid noise, different filters will be applied to both signals. Specifically, for the BVP signal, baseline drift will be removed by carrying out a 0.5-Hz cut-off-high-pass, linear phase finite impulse response (FIR) filter. Then, a 30-Hz cut-off low-pass, linear-phase FIR filter will be used to eliminate high-frequency noise and power-line interferences. Additionally, peaks related to pulse pumping will be located on BVP signals using a robust and reliable peak detection algorithm, capable of dealing with movement artefacts and signal morphologies [97]. Finally, interbeat intervals (IBIs) will be derived from the peak-data series.

Related to the SC signal, SC morphology is the result of two independent components: a fast-changing skin conductance response (SCR), overlapped with a slowly changing skin conductance level component (SCL). The SCL component ranges from 0 to 0.05 Hz, while SCR ranges from 0.05 to 1.5 Hz. Each SC signal will be filtered by applying a 1.5-Hz cut-off low-pass FIR filter to decrease noise generated during the acquisition.

Regarding heart rhythm, the IBI data series will be transformed to obtain the heart rate (HR) measured in beats per minute (BPM). Then, the HR metric will be partitioned into 5-s equally separated segments. Finally, the mean HR will be stored and used subsequently in the statistical analysis. A similar procedure will be carried out with the SC processed series. The data series will first be divided into equal segments lasting 5 s, and the mean of each segment will be recorded for subsequent analysis.
b)Data analysis

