We will calculate the mean SCL and HR values recorded for 4 min before the start of the negative mood induction procedure. These will be compared with the maximum scores obtained in the experimental phases (negative mood induction—viewing film clip—and emotional recovery using images). Independently for SCL and HR variables, repeated-measures ANOVA and post hoc Bonferroni tests will be performed in a mixed design with group (low, medium and high personal relevance groups) as between-subjects variable and time (pre-test—Time 1; post-negative emotional induction—Time 2; and postpositive emotional induction—Time 3) as within-subject variables.

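### Heart rate and skin conductance set a baseline mean against later phase maxima, so the time effect and both baseline contrasts come out significant without any change

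*Protocol article*

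**What the plan says.** The rule is in the protocol article, Statistical methods {20a}, under *Heart rate variability (HRV) and electrodermal activity (EDA)*, Data analysis.

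- Time 1: "We will calculate the mean SCL and HR values recorded for 4 min before the start of the negative mood induction procedure".
- Times 2 and 3: "These will be compared with the maximum scores obtained in the experimental phases", where the phases are the film clip and the picture recall.
- Model: "Independently for SCL and HR variables, repeated-measures ANOVA and post hoc Bonferroni tests will be performed in a mixed design", with image group between subjects and "time (pre-test—Time 1; post-negative emotional induction—Time 2; and postpositive emotional induction—Time 3) as within-subject variables".

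The Data processing part of the same section gives the likely unit for the maximum. HR is cut into 5-second segments, and for skin conductance "The data series will first be divided into equal segments lasting 5 s, and the mean of each segment will be recorded for subsequent analysis". The maximum itself is not defined further. The article gives neither a baseline maximum nor phase means for this comparison.

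Under *Experimental phase*, the film lasts 7 minutes and six pictures are shown for 1 minute each. *Objectives {7}* assigns the objective measures the role of backing up what the self-reports show.

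**The concern.** The three levels of the time factor are not the same quantity: one is a mean and two are maxima, over windows of three different lengths. A difference between Time 1 and either later time therefore mixes any real change with the gap between a maximum and a mean.

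Two readings are at stake. A Time 1 to Time 2 rise would be taken as autonomic confirmation that the negative induction worked, although it appears when nothing happens. At Time 3, a participant who has returned fully to baseline would still look aroused. That matters because the background under *Autonomic nervous system* says: "Low heart rate has been associated with pleasant or relaxed emotional states". A fall is thus one of the directions of interest.

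**Working it through.** **The plan's own figure.** None is given for the HR or SCL comparison. The planned total of 240 is taken as it stands, and the result does not depend on it.

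**Inputs from the article.** Taking 5-second segment means as the unit:

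- baseline: 240 s / 5 s = 48 segments
- film: 420 s / 5 s = 84 segments
- pictures: 360 s / 5 s = 72 segments

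**Assumptions, not in the article.** Segment values are normal and stationary with a lag-1 autocorrelation between 0 and 0.98. The within-person SD is 3 bpm. The SD only scales the offset.

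**Hand check at autocorrelation 0.** The expected maximum of n independent normal values is about Φ⁻¹((n − 0.375)/(n + 0.25)) SD above the mean.

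- Film: Φ⁻¹(83.625/84.25) = Φ⁻¹(0.9926) ≈ 2.44 SD, about 7.3 bpm.
- Pictures: Φ⁻¹(71.625/72.25) = Φ⁻¹(0.9913) ≈ 2.38 SD, about 7.1 bpm.

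**Simulation with no true change.** The planned mixed ANOVA (3 groups × 3 times) was run at N = 240 and alpha 0.05, with 300 runs per setting and no sphericity correction.

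| Autocorrelation | Film max − baseline mean (bpm) | Pictures max − baseline mean (bpm) | Time effect rejected, as planned | Time effect rejected, means throughout | Film vs pictures rejected at 0.05/3 | Group × time rejected |
|---|---|---|---|---|---|---|
| 0 | 7.34 | 7.16 | 100% | 3% | 15% | 7% |
| 0.5 | 7.14 | 6.95 | 100% | 7% | 16% | 5% |
| 0.8 | 6.50 | 6.29 | 100% | 9% | 17% | 5% |
| 0.9 | 5.76 | 5.51 | 100% | 6% | 19% | 5% |
| 0.95 | 4.80 | 4.57 | 100% | 8% | 12% | 5% |
| 0.98 | 3.54 | 3.32 | 100% | 7% | 12% | 6% |

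In SD units the offset runs from 3.32/3 = 1.1 to 7.34/3 = 2.4. The time effect was also rejected in 100% of runs at N = 24, 60 and 120 (autocorrelation 0.8).

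**Baseline contrasts.** Paired t-tests at 0.05/3 with 40 people (autocorrelation 0.8 or 0.9, 400 runs) were falsely significant in 100% of runs for maximum against mean. For mean against mean the rates were 1.75% (film) and 1.5% (pictures).

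**A true fall during the pictures.** The expected Time 3 − Time 1 difference is offset + true change. At autocorrelation 0.8 the offset is 6.29 bpm.

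| True change (bpm) | Offset + change | Simulated |
|---|---|---|
| −2 | +4.29 | +4.28 |
| −3 | +3.29 | +3.27 |
| −5 | +1.29 | +1.28 |
| −6 | +0.29 | +0.27 |
| −8 | −1.71 | −1.73 |
| −10 | −3.71 | −3.74 |

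**Film against pictures.** Both are maxima, so most of the offset cancels. The 84-segment window still gives a maximum 0.18 to 0.25 bpm higher than the 72-segment window (0.06 to 0.08 SD). That is enough for the 12% to 19% false rejection at N = 240, against 0.05/3 = 1.7%. This contrast detected every fall in the table above in 100% of runs.

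**Between randomised groups.** At Time 3, (offset + change in group A) − (offset + change in group B) = change in A − change in B. The common offset drops out, which agrees with the 4% to 7% rejection of group × time (unrounded range).

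**The case against.** The strongest reply is that the trial asks whether picture types differ, and on that question the summary is the same in every arm. This stands: with no change, the group-by-time test kept about its nominal level. A reader might infer that a calming effect of personal photographs would be mistaken for arousal relative to the other arms. The article does not support that, because a larger fall in one arm keeps its sign and size in the between-arm comparison. It would be disturbed only if the arms differed in within-person variability, which is not shown.

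A reader might also infer that a maximum can never show a fall. That is too strong. The fall passes through at full size, and only the reference to baseline is shifted. Falls larger than the offset, and falls from film to pictures, remain visible.

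Peak reactivity is a legitimate measure. The background also links heart-rate acceleration to intense emotion, and more skin-conductance peaks to standardised images. So the fault lies in the missing baseline peak and the unequal windows, not in using a peak.

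HR and SCL are supporting measures in a study labelled exploratory, and the induction is checked by the second PANAS. This limits the reach of the error but does not make the baseline contrasts interpretable.

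On skin conductance, the only filter described is this: "Each SC signal will be filtered by applying a 1.5-Hz cut-off low-pass FIR filter". By the article's own bands this leaves the phasic range (0.05 to 1.5 Hz) in the signal. It is tempting to conclude that the analysed SCL is contaminated. But the filter's stated purpose is noise reduction, SCL is named as the analysed variable, and a condensed article may omit the separation step. This is a point to confirm, not an established error.

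**Conclusion.** The rule is wrong as written for the HR and SCL time main effect and for the Time 1 against Time 2 and Time 1 against Time 3 contrasts. All of these are significant when nothing changes. Falls below baseline smaller than the offset (about 1.1 to 2.4 within-person SD) are masked or reported as rises. The film-to-pictures contrast has a modest further bias from unequal windows.

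The direction of the error needs no assumption beyond some variation between segments. Its size rests on the assumed normal, stationary series, the autocorrelation range, and reading the maximum as the largest 5-second mean. A different definition of the maximum would change the size but not the asymmetry.

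The conclusion does not extend to the randomised group-by-time comparison or to the PANAS analyses.

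**What to change.** Use one summary over windows of equal length at all three times, for example the mean of the 5-second segments. Name in advance which part of the film and picture phases supplies the window. If a peak measure is kept, take the baseline peak as well, over the same window length. For peaks, equal length removes a bias. For means, unequal length does not shift the expected value, but it makes the variances unequal.

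State also that the analysed SCL is taken from the 0 to 0.05 Hz band, or describe how it is separated from the phasic response.

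The cost is a sentence or two of analysis wording and no new data. A mean is less sensitive to a single brief peak, and matching the 4-minute baseline leaves 3 of the 7 film minutes and 2 of the 6 picture minutes out of this comparison.

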##### EEG signal

Data processing

The EEG recordings will be analysed off-line using custom software written in MATLAB. This custom software will be based on EEGLAB tools [98]. EEG functions will be used to clean the EEG-data. The EEG data will be segmented based on the event types. Fast Fourier transformation will be applied to an EEG epoch consisting of the time windows of 30 s each after the onset of the stimulus (film and images). Fourier transformed signals will then be averaged across event types. For further analysis, left frontal (F3, F7, FC5) and right frontal (F4, F8, FC6) electrode pools will be formed by averaging the frequency distributions of these signals. The mean magnitude of delta (0.5–4 Hz), theta (4.5–7.5 Hz), alpha (8–12.5 Hz), beta (13–30 Hz) and gamma (30.5–60 Hz) frequency band activities will be calculated for each participant during each event type.
b)Data analysis

A repeated-measures ANOVA will be performed to examine the possible effects of the intervention group (between-subjects variable) and time (within-subject variable) on the frequency band oscillations from frontal electrodes and on laterality (left vs right) by also examining the frequency band oscillations.

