The objective measures of emotion (EEG, EDA and HRV) will be used to substantiate the effects of emotion induction mechanisms observed in self-evaluations.

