**Fig. 2 Fig2:**
[figure not shown]
Experimental phase

At the start of the experiment, all the participants will be asked to complete the PANAS mood state scale [88]. This scale will be completed on three occasions: at the start of the task, following the negative mood induction (viewing the film clip) and after the autobiographical memory task (presentation of images according to the assigned experimental condition).

After completing the PANAS [88], the negative mood induction phase will begin. The participants will watch a 7-min section of the film “Dead Man Walking” (Polygram Filmed Entertainment, Havoc, Working Title Films), which shows the execution of a prisoner sentenced to death. Before seeing the film clip, the participants will be encouraged to experience the feelings generated by the clip as intensely as possible. After viewing the film clip, they will be asked to answer the control questions related to their level of concentration while watching the clip, and the degree to which they surrendered to the feelings it generated. They will then be asked to complete the PANAS [88] again in order to assess the effectiveness of the negative mood induction procedure.

Following the negative mood induction phase, the emotional recovery phase will be initiated, in which the participants will look at a total of six pictures previously selected according to their experimental condition in order to generate specific positive autobiographical memories. Each image will be presented for 1 min, and during this time, the participants will be asked to concentrate as hard as they can on the memory that each picture evokes with the aim of reliving the positive emotions they felt at that moment as intensely as possible. After each picture, the participants will answer a series of control questions related to their level of concentration while looking at the pictures and to what extent they were able to relive the emotions they felt at the moment related to the images. At the end of this phase, participants will once more complete the PANAS [88] in order to assess the effectiveness of the emotional recovery.

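### The EEG 'time' factor, as its epochs are described, can only contrast film with pictures, so its main effect cannot be used as support for mood induction or recovery

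*Protocol article*

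**What the plan says.** In the protocol article, section 'EEG signal', recordings are segmented by event type and the Fourier transform is applied to "time windows of 30 s each after the onset of the stimulus (film and images". Delta, theta, alpha, beta and gamma "frequency band activities will be calculated for each participant during each event type". The ANOVA then examines "possible effects of the intervention group (between-subjects variable) and time (within-subject variable) on the frequency band oscillations from frontal electrodes", and laterality. The section does not list the levels of time, describes no epoch before the film, and does not name the group by time interaction.

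The section 'Experimental phase' describes the two stimuli. For the negative induction, "The participants will watch a 7-min section of the film". For the recovery, six pictures are shown for 1 min each, and "the participants will be asked to concentrate as hard as they can on the memory that each picture evokes". The film always comes first.

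The section 'Objectives {7}' states that the objective measures, EEG included, "will be used to substantiate the effects of emotion induction mechanisms observed in self-evaluations". The Methods paragraph of the Abstract lists the EEG signal among the measures compared between groups before the induction, after it, and after the positive recall.

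**The concern.** A within-subject factor called time suggests the same measurement repeated as mood changes. PANAS fits that description: the same questionnaire is completed at three points. The EEG factor does not. Its two available levels differ in sensory input (moving clip or still image), in task (watching or deliberately recalling a personal event) and in position in the session, as well as in intended mood. Band power may differ between them for any of these reasons. The article's own background links gamma to cognitive processes, links alpha, delta and theta to arousal, and gives memory search and re-experiencing different lateralisation.

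The plan names the time effect as one to be examined and gives the EEG a corroborating role. A significant film-picture difference could then be read as objective confirmation that the induction and the recovery worked, although the contrast cannot separate that explanation from the others. The term that bears on the research question, whether image types differ in their change from film to pictures, is not named.

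**Working it through.** **Which levels the factor can have.** The two physiological sections, side by side:

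| | SCL and HR | EEG |
|---|---|---|
| Before induction | "We will calculate the mean SCL and HR values recorded for 4 min before the start of the negative mood induction procedure" | no epoch described |
| Film | maximum during the phase | 30-s windows after film onset |
| Pictures | maximum during the phase | 30-s windows after image onset |
| Levels of time | "time (pre-test—Time 1; post-negative emotional induction—Time 2; and postpositive emotional induction—Time 3) as within-subject variables" | not listed |

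Two levels is thus an inference, but film against pictures is the only within-subject contrast the described EEG processing can supply. If three levels were intended, Time 1 has no epoch. Adding one would still leave the step from Time 2 to Time 3 as film against pictures.

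**What the contrast contains.** For one band, the mean picture-minus-film difference is

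D = (mood) + (stimulus) + (task) + (order).

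Every participant has the same sequence, so no second equation separates these terms. The time main effect tests D = 0. For two image-type arms A and B, D_A − D_B removes whatever is common to both arms. All arms see the same film, then still pictures under the same recall instruction, so the general film-to-picture shift cancels. The comparison of arms during the pictures is randomised too and does not use the film at all.

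**Illustration of size.** The plan states no EEG figure to reproduce and gives no EEG variance. The shifts below are assumptions.

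*Inputs:* n = 240 (two age groups of 120, 'Sample size {14}'); two-sided 5% level; no mood effect; d = stimulus-driven shift divided by the SD of the within-person difference.

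*Formula:* noncentral t with df = 239 and noncentrality d × √240, where √240 = 15.49.

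| d | Noncentrality | Probability that the time effect is significant, per band |
|---|---|---|
| 0.10 | 1.55 | 34% |
| 0.15 | 2.32 | 64% |
| 0.20 | 3.10 | 87% |
| 0.30 | 4.65 | 99.6% |

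*Second check:* a simulated mixed ANOVA with three arms of 80 (240/3), two levels and 4,000 runs. It assumes a within-person correlation of 0.8 and no mood effect; the shift is in units of the raw SD.

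| Shift (raw SD) | Time significant | Group by time significant |
|---|---|---|
| 0 | 5.3% | 5.3% |
| 0.1 | 69% | 5.3% |
| 0.2 | 99.8% | 4.9% |
| 0.3 | 100% | 5.1% |
| 0.5 | 100% | 5.2% |

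The two scales agree. The SD of the difference is √(2 × (1 − 0.8)) = 0.632, so raw shifts of 0.1 and 0.2 equal d = 0.158 and 0.316. The noncentral t gives 68% and 99.8% for these.

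**The case against.** The strongest reply has five parts.

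- **The levels are not stated.** Elsewhere in the article time has three levels including a pre-test, the Abstract speaks of a before measurement, and a fuller protocol may define more epochs. This stands as a limit on wording: film against pictures is inferred. It does not rescue the factor, because a baseline would leave the film-picture step confounded.
- **The misuse is not planned.** A reader might infer that the protocol commits to reporting the EEG time effect as proof of mood change. It does not. It names two factors without saying which term carries the conclusion, a mixed ANOVA normally includes the interaction, and the stated aims concern differences between image types. What remains is that the plan names the confounded effect, leaves the interaction unnamed and assigns the EEG a corroborating role.
- **The randomised comparisons are sound.** A reader might infer that the EEG analysis as a whole is invalid, or that only the interaction is protected by randomisation. Neither is so. The group comparison during the pictures and the group main effect are also randomised contrasts.
- **Mood may contribute.** A reader might infer that the time effect reflects only the change of stimulus. The documents do not show that; they show only that mood cannot be isolated.
- **The problem is not peculiar to EEG, and the shifts are assumed.** Both are fair. The SCL and HR contrasts also cross rest, film and pictures, and even PANAS carries order and repetition. The calculation shows that 240 people would detect a small shift, not that one exists. The argument does not rest on it.

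The exploratory label in 'Trial design {8}' lowers the stakes but does not make the contrast interpretable as mood.

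**Conclusion.** The point holds in a limited form. With the epochs as described, the EEG time factor can only contrast film with pictures, and in that contrast mood is inseparable from stimulus, task and fixed order. Its main effect cannot support the claim that mood was induced or recovered. The randomised comparisons of image type, as group by period and as groups during the pictures, are unaffected.

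The conclusion rests on reading the film and image onsets as the full set of epochs, which is all the section gives. No size can be derived from the documents. Under assumed shifts of 0.1 to 0.3 SD of the difference, the chance of a significant time effect without any mood change runs from 34% to 99.6% per band, while the simulated group by time test stays near 5%. EEG is a supporting measure in an exploratory trial, so this is a correction worth making and not a threat to the main comparison. Separately, the EEG section and the Abstract do not agree on whether there is a pre-induction EEG measurement.

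**What to change.** In the section 'EEG signal':

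1. Label the within-subject factor period, with levels film and pictures.
2. Name image type by period (and by hemisphere), together with the image-type comparison during the pictures, as the EEG tests of interest.
3. State that the period main effect is descriptive and is not counted as evidence of mood change under 'Objectives {7}'.
4. Reconcile the section with the Abstract: define a pre-induction EEG epoch, or state that there is none. If one is defined, the film-picture contrast remains descriptive.

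Items 1 to 3 change analysis wording only and need no new data. Item 4 is also wording if no pre-induction epoch is claimed or if the headset already records before the film; the article does not say whether it does.

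A like-for-like EEG comparison within persons, such as a 1-min fixation screen after the film and after the sixth picture, is optional. It would add about 2 minutes per session, slightly delay the PANAS and still carry order effects. The fix does not need it.
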